4. MATERIALS AND METHODS

4.1. Study design:

This is a randomized, open, parallel-group clinical trial to investigate the safety and efficacy of a new cervical device called DUDA (Uterine Device for Dilatation of the Endocervical Canal). As this is an intervention in which the doctor must know the result of the randomization for implantation of the device, he will not be blind. The study will be carried out sequentially in two stages, the first being intended to exclusively evaluate the safety of using the device and the second to evaluate safety and effectiveness.

4.2. Study Location:

The study will be carried out in the Oncology and Prevention Gynecology Departments of the Barretos Cancer Hospital/Pio XII Foundation (Barretos, SP).

4.3. Inclusion criteria:

For inclusion, all criteria must be present:

a) Histopathological diagnosis of NIC2/3 on cervical biopsy;

b) Indication for performing CAF (high-frequency surgery);

c) Age between 18 and 65 years;

4.4. Exclusion criteria:

For exclusion, any of the following criteria must be present:

a) Pregnant women before CAF;

b) Previous conization / CAF history;

c) Women who do not understand or accept the study;

d) Women subjected to a regime that determines significant vulnerability to the participant (ex: prisoners, indigenous, etc.)

4.5. Description of the Endocervical Canal Dilatation Device (DUDA):

It is a plastic device (polyacetal) designed by the responsible researcher, made by hand on a lathe through the wear of a cylindrical part.

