4.9.2. Second step: analysis of the effectiveness

The participants in the first stage will not be part of the second. Although the main objective of this step is to evaluate the effectiveness of the device in preventing post-conization cervical canal stenosis, safety and quality of life issues will also be analyzed. The observation period for the second stage will be two years.

In the second stage, 240 participants will be recruited randomly balanced 1: 1 in two groups: one who will receive the DUDA device after CAF and another who will not receive it. Randomization, active search and patient management will take place at the outpatient clinic after the signature of the TLCE by the nurse responsible for clinical research in the department and will be carried out in blocks of 4, through the REDCap program.

4.10. Study outcomes:

4.10.1. Device security:

The safety analysis will be performed up to 30 days after surgery. The definitions of CTCAE (Common Terminology Criteria for Adverse Events) version 4.0 will be adopted as a reference for the security assessment of the device. For that, two main safety events will be considered during its use: vaginal bleeding and uterine infection. Below are the gradations for the two main security events defined by CTCAE version 4.0.

a) Vaginal bleeding:

- Grade 1: mild bleeding, identified on clinical examination or imaging study. No intervention is indicated;
- Grade 2: moderate bleeding; Medical intervention is indicated;
- Grade3: bleeds, intense; need for a blood transfusion; radiological or endoscopic intervention is indicated;
- Grade 4: bleeding determines life-threatening; urgent surgical intervention is indicated;
- Grade 5: death from bleeding.

b) Uterine infection:

- Grade 1: (there is no category for this event);
- Grade 2: moderate symptoms; oral intervention is indicated (eg: antibiotics, antifungal, antiviral);
- Grade 3: intravenous intervention is indicated (eg: antibiotics, antifungal, antiviral); radiological intervention or surgical intervention are indicated;
- Grade 4: infection determines life-threatening; urgent surgical intervention is indicated;
- Grade 5: death from bleeding.

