5. SAMPLE CALCULATION

5.1. First step:

For the safety analysis of the device, 25 women will be included, as advised by the National Ethics and Research Commission (CONEP).

5.2. Second stage:

The sample calculation assumed the premise of a cervical canal stenosis rate of approximately 15% to 20% after the CAF described in the literature and reduced to 6% with the use of an endocervical device according to the uncontrolled trial by Luesley et al (11) Considering this difference in stenosis rates (15-20% vs. 6%), an alpha error of 5%, a beta error of 20% and a balanced allocation 1: 1, the sample estimate ranges from 104 to 203 in each group. Therefore, this stage of the study will recruit 120 women in each arm, totaling 240 participants.

It is estimated that recruitment will take place between 1 to 3 weeks in the first stage and between

25 to 30 weeks in the second stage, since the potential for recruitment is 06 to 10 surgeries per week.

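### A single block size of 4, written into the protocol of an open single-hospital trial, makes one third of allocations deducible in advance; undisclosed varying block sizes would be a cheap improvement

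*Protocol*

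**What the plan says.** Protocol Section 4.1 describes the design: "This is a randomized, open, parallel-group clinical trial". It adds that the doctor must know the allocation in order to place the device. Section 4.2 names one hospital: "The study will be carried out in the Oncology and Prevention Gynecology Departments of the Barretos Cancer Hospital/Pio XII Foundation".

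Section 4.9.2 sets the allocation for the second stage: "In the second stage, 240 participants will be recruited randomly balanced 1: 1 in two groups". On method it says that randomisation "will be carried out in blocks of 4, through the REDCap program". No other section gives a second block size, a stratification factor, or a statement that the size is kept from the staff who enrol.

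On who does what, Section 4.9.2 says: "Randomization, active search and patient management will take place at the outpatient clinic after the signature of the TLCE by the nurse responsible". The nurse meant is the department's research nurse. Section 4.12.1 has eligible women invited and consented at the initial visit, without saying who invites them. One exclusion in Section 4.4 leaves room for judgement at that point: "Women who do not understand or accept the study".

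**The concern.** In a 1:1 block of 4, each arm has two places. Once one arm has filled its two, the rest of the block is settled. In an open trial at one hospital, past allocations are visible, and the protocol itself supplies the block size needed to read them. Concealing the list in REDCap and randomising after consent are sound precautions, but neither prevents deduction from what has already been allocated.

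The pace makes a tally easy to keep. Section 5.2 expects 6 to 10 surgeries a week, so a block fills in a few days (6/4 = 1.5 to 10/4 = 2.5 blocks a week). Moving one woman's enrolment a little earlier or later could change the slot she receives.

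What is at stake is the comparability of the arms in the primary comparison. If someone who can foresee the next arm also has a say in who is enrolled or when, women thought more or less likely to develop stenosis could be distributed unevenly. Section 6 compares stenosis rates with an unadjusted chi-square or Fisher test. An adjusted analysis would reach only the factors that were recorded.

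**Working it through.** **Inputs.** Block size 4, 240 women, ratio 1:1 (Section 4.9.2), so 240/4 = 60 blocks. The protocol gives no predictability figure to reproduce. Its sample size in Section 5.2 (104 to 203 per group) does reproduce, using a two-sided 5% level, 80% power and a continuity correction, and is not affected by this point.

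**Allocations known with certainty.** Call the arms A and B. A 2:2 block has 6 equally likely sequences:
- AABB and BBAA: the first two match, so places 3 and 4 are certain (2 places each).
- ABAB, ABBA, BAAB and BABA: only place 4 is certain (1 place each).

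Mean certain places per block = (2×2 + 4×1)/6 = 8/6 = 1.333. Share = 1.333/4 = 33.3%. Expected number = 60 × 1.333 = 80 of 240.

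The number over 60 blocks is 60 plus a binomial count (60 blocks, probability 1/3). Its standard deviation is √(60 × 1/3 × 2/3) = 3.65, so a 95% range is 80 ± 1.96 × 3.65, or about 73 to 87.

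**Best-guess accuracy.** The observer always guesses the arm that is behind in the current block, and tosses a coin when the arms are level:
- Place 1: 1/2.
- Place 2: 2/3.
- Place 3: 1/3 × 1 + 2/3 × 1/2 = 2/3.
- Place 4: 1.

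Mean = (1/2 + 2/3 + 2/3 + 1)/4 = 17/24 = 70.8%, or 170 of 240, against 50% with no information.

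**Alternatives.** Single fixed sizes were enumerated in the same way. Mixed sizes were simulated: 240 allocations, 300 repeats, each size equally likely. The observer knows the set of sizes but not their order, and updates the probabilities after each allocation.

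| Scheme | Certain in advance | Best guess correct |
| --- | --- | --- |
| Fixed 4 (as written) | 33.3% | 70.8% |
| Fixed 6 | 25.0% | 68.3% |
| Fixed 8 | 20.0% | 66.6% |
| Random 4 and 6 | 5.3% | 69.3% |
| Random 4, 6 and 8 | 2.5% | 68.0% |

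Mixing sizes therefore removes nearly all certain knowledge, even if the set of sizes leaks, but only a small part of the guessing advantage. With 4, 6 and 8, the excess over chance falls from 20.8 to 18.0 points, a cut of 2.8/20.8 = 13.5%.

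**The case against.** **The role of the nurse.** A reader might infer from Section 4.9.2 that one nurse finds the candidates, randomises them and manages them, so that the person able to predict the next arm also decides who is approached. The sentence does not establish this. The mention of the nurse may belong only to the signing of the consent form. The active search is placed after consent, so it may mean tracing participants rather than finding candidates. This objection stands: that the nurse can influence enrolment is a possible reading, not a stated fact.

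**When the arm is known.** A reader might also infer that a third of allocations are known before the woman is approached. The deduction needs a complete tally in order of randomisation. The documents name two departments within the hospital and do not say who sees every allocation. A surgeon sees the arms in order of surgery, and a count of devices placed would be disturbed by the cases in Section 4.8 where the device is withheld after randomisation. The one third is therefore what a full observer can know, not what any named person does know.

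**Size of the bias.** It is tempting to put a number on it from the relative risk of 5.07 for wide endocervical excision in Section 1.1. That would need the share of such women and the degree of steering, and the protocol gives neither. Widening into the canal is also an operative feature (Section 4.6, step 8), only partly foreseeable at enrolment. No such number is supported.

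**Limited gain.** Someone willing to steer could act on a best guess, and varying sizes barely reduce that. This is true and limits the benefit. It does not defeat a change that costs almost nothing and removes most of the certain knowledge.

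**Silence on stratification.** Strata may exist that the protocol does not mention. They would leave the share at one third in completed blocks for anyone who tracks each stratum.

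**Conclusion.** The point holds as a cheap improvement. The protocol fixes one small block size and discloses it in an open trial at one hospital. For an observer who sees all allocations in order, 33.3% are certain in advance (about 80 of 240, 95% range about 73 to 87) and 70.8% can be guessed correctly. These figures are exact for completed blocks of 4.

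Whether this leads to selection bias depends on whether such an observer also influences enrolment, which the protocol leaves unclear. If so, the bias could not be reliably removed afterwards, because adjustment covers only measured factors. Nothing in the documents shows that steering would occur, and they give no basis for estimating how large its effect would be.

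**What to change.** In Section 4.9.2, replace the stated block size with a sentence saying that randomisation uses randomly permuted blocks of varying size. Put the sizes in a restricted document held by a statistician outside the clinic, who prepares the allocation table and loads it into REDCap. The clinic's randomisation procedure need not change. It would also help to state who invites the women and who performs the randomisation, so that the sentence about the nurse has one meaning.

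The cost is one protocol sentence and one new allocation table. With blocks of up to 8, the running imbalance between arms can reach 4 women instead of 2, which is negligible for 240. The change removes most certain knowledge of the next allocation. It does not make the sequence unpredictable.

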3) Asepsis with degerming iodine throughout the perineal and vaginal region. If the patient has an allergy to iodine, asepsis is performed with chlorhexidine gluconate solutions;

4) Placement of sterile surgical drapes;

5) Introduction of the vaginal speculum and identification of the cervix;

6) Passage of acetic acid and Lugol´s iodine in the cervix and vaginal walls to identify positive acetowhite and iodine areas;

7) Local anesthesia with 2% lidocaine with a vasoconstrictor, infusing 2 ml in each quadrant of the cervix (3, 6, 9 and 12h);

8) Passage of the diathermic loop connected to the generating source in “cut” mode (level 60) in a single pass, with or without enlarging the endocervical canal (depending on the indication of each case);

9) Hemostasis with a "ball" electrode connected to the generating source in "coagulation" mode (level 60).

After this surgical procedure, the patient remains in the hospital for a few more hours for recovery from anesthesia and observation of eventual postoperative bleeding. The patient is discharged from the hospital with guidance on the use of analgesics (if necessary) and to abstain from sexual intercourse for at least 30 days due to the risk of bleeding during intercourse.

4.7 Procedure for placing the endocervical device (DUDA):

After the end of the CAF, and with the patient still positioned on the operating table, the surgeon will place the DUDA device on the cervix. Device deployment is quick and requires no more than 5 minutes. It should be noted that this procedure represents the experimental part of the study.

The surgeon will carefully insert the nail into the endocervical canal until the flat circular surface of the device rests on the cervix. By means of the simple suture in four points (2-0 polypropylene thread, atraumatic needle), the device will be fixed to the surface of the cervix. In the event that the residual neck has a very flat surface, the device may be attached to the lateral fornices.

4.8 Criteria for not placing or removing the device:

Even if the participant has signed the Free and Informed Consent Form and the randomization has already been carried out, the DUDA device will not be placed on patients who have any complications during the performance of the CAF and that require additional procedures, such as bed bleeding. surgical procedure requiring hemostatic procedures with suture and/or use of a vaginal tampon.

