At the time of the initial visit, preoperative tests (blood count, serum biochemistry, coagulogram, chest X-ray, electrocardiogram and pregnancy test) and pre-anesthetic evaluation of women in whom CAF is indicated will be checked. This preoperative assessment is done on a routine basis and does not include specific aspects of the study. Women who are eligible for CAF and meet the study's eligibility criteria will be invited to participate in the survey. Those who agree will sign the Informed Consent Form at the initial visit.

During this visit, demographic and clinical information will be collected through interviews and consultation of medical records (Annexes 3). At this time, the quality of life questionnaires will also be applied.

4.12.2. Operative and postoperative visits:

On the day of surgery, a form will be filled out with the data pertinent to the surgical procedure. (Annex 4).

Postoperative visits will take place 15 days (1-PO) and 30 days (2-PO) after surgery. (Annexes 5 and 6). The acceptable windows of opportunity for visits will be ± 3 days. During these visits, the participants will undergo a medical consultation, when anamnesis and gynecological physical examination will be carried out. They will also answer the quality of life questionnaires. Any adverse event will be recorded on a specific form each post-operative visit in accordance with the Common Terminology Criteria for Adverse Events v3.0 (CTCAE V3). (Annex 7).

Participants who have the DUDA device will have it removed during the 2-PO visit during the gynecological examination.

4.12.3. Follow-up visits:

Follow-up visits will take place 3, 6, 12 and 18 months after surgery (respectively FUP-1, FUP-2, FUP-3 and FUP-4) according to our flow chart described below. The acceptable windows of opportunity for visits will be ± 10 days. During these visits, participants will undergo a medical consultation, when anamnesis and gynecological physical examination will be performed, which will include the collection of material for cervical cytology, hysterometry to assess the permeability of the endocervical canal and colposcopy to visualize the squamocolumnar junction. The degree of permeability of the channel will be recorded in a specific form. During follow-up visits, quality of life questionnaires will also be applied and adverse events will be recorded and follow-up information will be collected (Annex 8-11).

4.12.4. Surgery information:

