The researcher will record the surgical times for carrying out the CAF and for implanting the device. Such records will be performed separately following the datasheet at the time of surgery.

TABLE 1 - Summary of study activities according to the moment.

|  | ***Baseline*** | **Surgery** | **1- FUP** | **2-FUP** | **FUP-1** | **FUP-2** | **FUP-3** | **FUP-4** |
| --- | --- | --- | --- | --- | --- | --- | --- | --- |
| **Moment** | - | Day 0 | 15 days | 30 days | 3 months | 6 months | 12 months | 18 months |
| **Time of delay** | - | - | ± 3 days | ± 3 days | ± 10 days | ± 10 days | ± 10 days | ± 10 days |
| **Elegebility** | X |  |  |  |  |  |  |  |
| **Consent Information** | X |  |  |  |  |  |  |  |
| **Randomization** | X |  |  |  |  |  |  |  |
| **Surgery (LEEP)** |  | X |  |  |  |  |  |  |
| **Device** |  | X |  |  |  |  |  |  |
| **Medical History** |  |  | X | X | X | X | X | X |
| **Gynecologic exam** |  |  | X | X | X | X | X | X |
| **Time of remove device** |  |  |  | X |  |  |  |  |
| **Pap smear** |  |  |  |  | X | X | X | X |
| **Hysterometry** |  |  |  |  | X | X | X | X |
| **Colposcopy** |  |  |  |  | X | X | X | X |
| **QOL** | X | X | X | X | X | X | X | X |
| **Adverse events** |  |  | X | X | X | X | X | X |

FICT = Informed Consent Form, CAF = High frequency surgery, QOL = Quality of life, EA = Adverse event

NOTE: The safety analysis of the device will be performed until the 30th postoperative day.

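### The safety analysis closes 30 days after surgery, about when the sutured device is removed (day 30 ±3), so removal-related bleeding or infection is largely left out, in conflict with the window in 4.9.1

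*Protocol*

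**What the plan says.** Three places end the safety analysis 30 days after surgery:

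- Section 4.10.1: "The safety analysis will be performed up to 30 days after surgery".
- The note under Table 1: "The safety analysis of the device will be performed until the 30th postoperative day".
- The first note to the schedule in section 10, for the 25 women of stage 1.

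The first two name no stage. Section 4.10.1 adds a second restriction: "two main safety events will be considered during its use: vaginal bleeding and uterine infection".

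Section 4.12.2 gives the timing of removal: "Postoperative visits will take place 15 days (1-PO) and 30 days (2-PO) after surgery"; "The acceptable windows of opportunity for visits will be ± 3 days"; and "Participants who have the DUDA device will have it removed during the 2-PO visit during the gynecological examination". Under 4.7 the device is held by a four-point suture: "the device will be fixed to the surface of the cervix".

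Other passages look past day 30. Section 4.9.1 sets the stage-1 safety window as the period of device use plus 30 days from removal. Later in 4.10.1, other events thought to be device-related are to be graded whether they arise while the device is in place or afterwards. At the follow-up visits of 4.12.3 (3, 6, 12 and 18 months), "quality of life questionnaires will also be applied and adverse events will be recorded and follow-up information will be collected".

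**The concern.** Taking out a device stitched to the cervix is part of the intervention, and bleeding and infection are the two events the protocol singles out. The stated window ends at about the moment when removal could cause them. Safety is secondary objective 3.2.1, and stage 2 holds the trial's only controlled safety data. Removal happens only in the device arm, so any removal-related event that goes uncounted is lost from that arm.

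The restriction of the two main events to the period of use also has no meaning for women who receive no device, so it cannot define a comparison between arms. In stage 1, the same late event can count or not count depending on which section is applied, and stage 1 decides whether the trial proceeds.

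**Working it through.** **Inputs.** Cut-off: day 30 after surgery (4.10.1, Table 1 note, section 10 note). Removal day d: 30 ± 3, so 27 to 33 (4.12.2, Table 1). Stage-1 window in 4.9.1: closes on day d + 30.

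**Formulas.** Post-removal days inside the cut-off = max(0, 30 − d). The removal itself is inside only if d ≤ 30.

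| Removal day d | Removal inside day 30? | Post-removal days inside | Share of 30 days | Window closes under 4.9.1 |
|---|---|---|---|---|
| 27 | yes | 3 | 10% | day 57 |
| 28 | yes | 2 | 7% | day 58 |
| 29 | yes | 1 | 3% | day 59 |
| 30 | yes | 0 | 0% | day 60 |
| 31 | no | 0 | 0% | day 61 |
| 32 | no | 0 | 0% | day 62 |
| 33 | no | 0 | 0% | day 63 |

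For on-schedule removals the calendar rule therefore allows at most 3 post-removal days, against 30 under 4.9.1. If the restriction to the period of use is also applied strictly, bleeding and infection have no post-removal day at all, even when d is 27.

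**The rules applied to single records.**

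- Device removed on day 32, bleeding at removal: outside a literal day-30 cut. The same event with removal on day 28 is inside that cut.
- Device removed on day 30, uterine infection on day 35: outside 4.10.1 and the Table 1 note. In stage 1 it is also outside the section 10 note but inside 4.9.1, which runs to day 60.

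**Would FUP-1 cover the gap?** Take 3 months as 90 days (an assumption). With the ±10-day window, FUP-1 falls on days 80 to 100. The shortest time from an on-schedule removal is 80 − 33 = 47 days and the longest is 100 − 27 = 73 days. Both exceed the 30 days that 4.9.1 uses.

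**The case against.** The strongest reply is that day 30 and the 2-PO visit are the same nominal time point. Table 1 has one column for 30 days, with the ±3-day window and removal both marked in it, and 4.12.2 has adverse events recorded at that visit. On this reading the analysis runs through 2-PO, including the removal, and nothing says that a record from days 31 to 33 is discarded. This is a fair reading and it weakens the literal one. It does not bring in anything after the visit, and that is when an infection or delayed bleeding from removal would appear.

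A second reply is that later events stay in view. Section 4.10.1 grades other device-related events after use. Section 6 summarises adverse events without a day limit, the interruption rules in 4.11 have none, and the committee in section 7 watches safety throughout. All of this stands. But the two main events are the ones held to the period of use, and the interruption rules concern grades 3 to 5, so lower-grade bleeding or infection after removal could still drop out of the reported safety analysis.

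A reader might infer more than the protocol supports, in three ways:

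- **A fixed share lost.** Three of the seven permitted days lie after day 30, which suggests 3/7, or 43%, of removals. That needs removals spread evenly over the window and a hard calendar cut. The protocol gives no distribution; on the literal cut the share could be anything from 0% (all by day 30) to 100% (all later).
- **A demonstrated bias towards safety.** The direction follows for any removal-related event left out, but the amount depends on a complication rate that is not given. The uncontrolled study of 33 women cited in 8.3 reported no bleeding or infection complications, and section 6 plans confidence intervals for adverse events without naming a between-arm test.
- **A stage-2 problem only.** Section 4.10.1 and the Table 1 note are not confined to stage 2, and the section 10 note contradicts 4.9.1 for stage 1.

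**Conclusion.** The point holds as a conflict between stated rules, not as missing detail. As written, the safety analysis ends about when the device comes out. At most 3 days after an on-schedule removal are inside it, and none for bleeding and infection if the restriction to the period of use is applied strictly. Section 4.9.1 sets 30 such days for stage 1.

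The day counts rest only on the protocol's own dates and assume removal within the 2-PO window. Women whose device is removed early under 4.8 would have more than 3 post-removal days before day 30. The exclusion of removals on days 31 to 33 depends on the literal reading; the exclusion of the period after 2-PO does not.

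The number of events lost is unknown. What is affected is the reported safety analysis for objective 3.2.1, not the collection of data. The correction should be made because it is cheap and bears on a stated objective, but the primary effectiveness analysis is untouched.

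**What to change.** Reconcile 4.9.1, 4.10.1, the Table 1 note and the section 10 note on one analysis window per stage, each including removal and a period after it.

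- **Stage 1:** carry the analysis window already in 4.9.1 (device use plus 30 days after removal) consistently through the other places.
- **Stage 2:** state a window identical in both arms, for example surgery through FUP-1. Report it as surgery to 2-PO, bounded by the visit and not by day 30, and 2-PO to FUP-1.
- **Both stages:** delete the restriction of the two main events to the period of use.

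This changes what is analysed, not when or how the device is removed. The cost is wording: adverse events are already recorded at FUP-1 in both arms, so no new visit or form is needed.

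There are two small drawbacks. More background bleeding enters both arms. No visit is scheduled between 2-PO and FUP-1, so events in that interval rest on recall at FUP-1 or on spontaneous report. For stage 1, the text should say how events up to day 57 to 63 are ascertained before the safety report is made.

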Other events in which the researcher believes that there is a possible, probable or definitive relationship with the device (during or after its use) other than the two mentioned above will also be classified according to CTCAE version 4.0. Information about all adverse events provided voluntarily by the research participant, discovered by the researcher's questions or detected by physical examination, laboratory tests or other means, will be collected, recorded in the medical record and monitored as appropriate.

Clinical conditions/illnesses present before starting study treatment are considered adverse events when they worsen after the start of study treatment (any procedure specified in the protocol). Adverse events that occur before the study treatment begins, but after signing the informed consent form will be recorded in the medical record. Laboratory values ​​or abnormal test results are only adverse events if they induce clinical signs or symptoms or require therapy, and will also be recorded. The data of adverse events will be extracted from the original documents, reviewed by the responsible researcher and inserted in the study database. For the purposes of this study, the following definitions will be considered:

• Adverse event: any undesirable sign, symptom or clinical condition that occurs after the start of study therapy, even if it is not considered to be related to study therapy.

• Serious adverse event: any medical event that results in: death, adverse life-threatening surgical experience, hospitalization or prolonged hospitalization, persistent or significant disability/disability, or congenital anomaly. Important medical events that do not result in death, are life-threatening or require hospitalization can be considered as serious when, based on the appropriate clinical opinion, put the patient at risk or require medical or surgical interventions to avoid one of the results indicated in this definition.

4.10.2. Efficiency:

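### Sections 4.10.1 and 4.12.2 of the protocol contradict each other on which stage 2 adverse events are graded, and by which CTCAE version

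*Protocol*

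**What the plan says.** Section 4.10.1 (Device security) defines the safety outcome. It sets a window of 30 days from surgery, takes CTCAE v4.0 as its reference, and says that "two main safety events will be considered during its use: vaginal bleeding and uterine infection". It then extends classification to "Other events in which the researcher believes that there is a possible, probable or definitive relationship with the device (during or after its use"; events of this kind "other than the two mentioned above will also be classified according to CTCAE version 4.0".

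The same section has wider wording on collection. Information on all adverse events "will be collected, recorded in the medical record and monitored as appropriate". On data entry it says: "The data of adverse events will be extracted from the original documents, reviewed by the responsible researcher and inserted in the study database". Its definition counts an event as adverse "even if it is not considered to be related to study therapy".

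Section 4.12.2, on the visits at days 15 and 30, says: "Any adverse event will be recorded on a specific form each post-operative visit in accordance with the Common Terminology Criteria for Adverse Events v3.0". It sets no condition on arm or relatedness. Section 4.12.3 and Table 1 have adverse events recorded at months 3, 6, 12 and 18 without naming a CTCAE version or asking for a grade.

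Stopping criterion 4.11(c) is triggered by two grade 3 or 4 events in the second stage, with no limit by arm, relatedness or day. Section 6 summarises adverse events as frequencies with 95% confidence intervals. Section 7 has the monitoring committee work from the collection forms and interim analyses.

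**The concern.** Safety is a secondary objective (3.2.1), and section 4.9.2 says that safety will also be analysed in stage 2. A comparison of safety between randomised arms is fair only if an event has the same chance of entering the graded set in each arm. A relatedness condition fails that test when one arm has no device. The trial is also open (4.1), so whoever applies the condition knows the allocation.

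The condition does little harm in stage 1, where all 25 women have the device and section 4.9.1 uses a similar one. Section 4.10.1 carries it into stage 2, where 120 women have no device. There it could work in either direction. Ordinary after-effects of the excision could be graded in device women only, or a real device effect could drop out because the researcher judged it unrelated.

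This is not detail that can wait for a statistical analysis plan. Which events are graded, in whom and by which version is settled when the forms are completed, and missing grades cannot be reliably recovered later.

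**Working it through.** The protocol gives no figure on this point to reproduce. The check sets its rules side by side.

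| Feature | 4.10.1 | 4.12.2 (days 15 and 30) | 4.12.3 (months 3–18) |
|---|---|---|---|
| Events other than bleeding and infection | Classified if at least possibly device-related | Any event | Recorded |
| Can a control woman's event qualify? | No | Yes | Yes, but no grading stated |
| CTCAE version | 4.0 | 3.0 | None named |
| Time covered | 30-day analysis window; attributed events also after use | To day 30 | After day 30 |

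**Step 1: only 4.10.1 followed.** Other events are graded only on attribution to the device, so the control arm supplies none.

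**Step 2: only 4.12.2 followed.** Any event in either arm is recorded by CTCAE at the two visits that cover the 30-day window. The one-sidedness does not arise, but the version differs from the one 4.10.1 takes as its reference.

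**Step 3: both followed.** A device-attributed event is classified by v4.0 and the same symptom in a control woman by v3.0.

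**Step 4: after day 30.** The device comes out at the 30-day visit. Because 4.10.1 reaches attributed events after use, it is the only grading rule stated for other events from then on, and it can apply only to women who had the device. The formal safety analysis has closed by then, but criterion 4.11(c) has no day limit and needs grades.

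**Step 5: bleeding and infection.** Counting these while the device is in use nearly matches the 30-day window when removal is on schedule (day 30 ± 3). It does not when the device is removed early or never placed, both of which 4.8 allows. A control woman has no period of use at all.

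**Illustration of step 1 only.** Assume the same true rate r of other events in both arms and a share q of device-arm events attributed to the device. Neither value comes from the protocol. Expected graded events are 120 × r × q in the device arm and 0 in the control arm. Fisher's exact p is in brackets, from counts rounded to whole events.

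| r | q = 25% | q = 50% | q = 100% |
|---|---|---|---|
| 5% | 1.5 v 0 (0.50) | 3 v 0 (0.25) | 6 v 0 (0.029) |
| 10% | 3 v 0 (0.25) | 6 v 0 (0.029) | 12 v 0 (0.0004) |
| 20% | 6 v 0 (0.029) | 12 v 0 (0.0004) | 24 v 0 (<0.0001) |

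For example, 120 × 0.20 × 0.50 = 12. The p-values only show scale, since section 6 names no between-arm safety test.

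**The case against.** A reader might infer from 4.10.1 that a control woman's other events can never be graded, so that her arm scores zero by construction. The protocol does not support this. Section 4.12.2 records any event in either arm by CTCAE, and its two visits cover the stated safety window. The relatedness sentence in 4.10.1 says that such events are also classified: it adds a class and does not say the rest go ungraded. Section 4.10.1 also sends adverse event data to the study database with no stated filter, and its definition does not require relatedness. Criterion 4.11(c) counts graded events without regard to arm. Pain is measured in both arms by the scales in 4.10.3 in any case.

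All of this stands, and it limits the point. It does not remove it. Entry in the database is not the same as grading, and no sentence says that events outside the relatedness condition are graded by the version 4.10.1 uses. Section 4.12.2 names another version, so it cannot simply be read as carrying out 4.10.1. It also says nothing about the period after day 30.

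It is also fair to say that a between-arm difference with its confidence interval may be specified in an analysis plan not shown here. Its absence is not part of this point.

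**Conclusion.** The contradiction is real and should be resolved before stage 2 data are collected. Sections 4.10.1 and 4.12.2 differ on which events are graded and by which CTCAE version. The protocol does not say which set feeds the safety analysis or the count in 4.11(c).

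The size of the effect depends on the reading. If 4.10.1 alone governs, the comparison of other events is attribution-dependent and one-sided. With half of device-arm events attributed, a device with no effect would show from 3 against 0 (5% background) to 12 against 0 (20% background). These are assumed rates, not trial data. If 4.12.2 governs, this asymmetry disappears within 30 days and only the version conflict remains. If both are followed, the arms may be graded by different versions. A biased safety comparison is therefore a risk that the text leaves open and not a settled feature of the plan.

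**What to change.** Reconcile 4.10.1, 4.12.2 and 4.12.3 so that, for stage 2:

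- every adverse event in both arms is graded by one named CTCAE version, on the same form, at every visit, whatever its attribution;
- bleeding and uterine infection are counted over the same days from surgery in both arms, and not by period of device use;
- causality is recorded as an attribute of each event, and device-related events are reported as a subset of all-cause rates by arm;
- the text states which event set feeds the safety analysis and which feeds the count in 4.11(c). This point takes no position on what that stopping criterion should be.

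The cost is mainly wording. Visits and adverse event recording are already scheduled for all participants in 4.12 and Table 1. If the follow-up forms have no field for grade, one must be added. The small downside is the work of grading some trivial events.
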